## Abstract

**Background:**

In subjects with hypercholesterolaemia, cholesterol values remain above guideline levels. One of the limiting factors to the achievement of goals in such patients is therapeutic non-adherence. The aim of this study is to assess the effectiveness of an intervention designed to improve control of hypercholesterolaemic patients, consisting of a combined strategy that would include the delivery of printed information, treatment-compliance check cards and the dispatch of text messages as complementary measures in support of the intervention at the general practitioner’s practice.

**Methods/Design:**

A randomised, parallel-group clinical trial will be conducted at the family medicine outpatient facilities of eight health centres in three of Spain’s Autonomous Regions (Comunidades Autónomas), covering a total of 358 subjects aged 18 years or over with diagnosis of hypercholesterolaemia. Patients in the intervention group will be supplied with printed material with information on the disease and its management, mobile-telephone text messages with guideline summaries, reminders of forthcoming appointments and/or arrangements for making new appointments in the event of non-attendance, and self-report cards to check compliance with recommendations. Both groups -intervention and control- will receive routine recommendations from their physicians in accordance with current European clinical practice guidelines for hypercholesterolaemia and cardiovascular risk management. As regards the measurements to be made, the main variable is the proportion of subjects who attain the low density lipoprotein cholesterol levels set as a target across a follow-up period of 24 months. The secondary variables are as follows: adherence to recommendations on lifestyle and adherence to drug treatment; variation in lipid profiles and cardiovascular risk levels; appearance of cardiovascular events; physical activity; food consumption; smoking habit; anthropometric measures; blood pressure; health problems; use of hypolipidaemic agents; socio-demographic data; beliefs and expectations about preventive recommendations; and degree of satisfaction with the combined strategy.

**Discussion:**

Should this intervention prove effective, a recommendation could be issued on the application of this combined strategy to subjects with hypercholesterolaemia. It is a simple, relatively inexpensive intervention.

**Trial registration:**

ClinicalTrials.gov: NCT02314663.

## Background

Hypercholesterolaemia is one of the main cardiovascular disease risk factors (CDRFs) and, according to different studies undertaken in Spain, its prevalence in terms of total plasma cholesterol concentrations of over 250 mg/dl, extends to 20%-23% of the adult population [1, 2].

The prevention and treatment of dyslipidaemia should take the remaining CDRFs into account, with its management being based on the calculation of cardiovascular risk. While most European clinical practice guidelines use a Framingham or Systematic Coronary Risk Evaluation (SCORE) function chart [3] for this purpose, the Registre Gironí del Cor (REGICOR) study [4] offers an alternative, using a series of tables adapted and validated in Spain. Management of dyslipidaemia includes both pharmacological and non-pharmacological measures (diet and physical activity), with the latter being recommended for 3 to 6 months in primary prevention prior to the introduction of hypolipidaemic treatment [5–7].

Furthermore, the degree of control of CVR (cardiovascular risk) factors is low, both in primary and in secondary prevention. Despite guidelines and new hypolipidaemic agents, the results of different studies nonetheless show that cholesterol values remain above guideline targets [8]. Studies, such as HISPALIPID [9] and PREVENCAT [10], have revealed poor control of subjects with dyslipidaemia, with the designated targets being attained in approximately 32% of cases. The EUROASPIRE II study reported that 64% of patients with coronary disease took hypolipidaemic agents, and that approximately 53% failed to display adequate therapeutic control [8]. Similar results as regards achievement of goals were reported by the international EUROASPIRE III [11] and LTAP-2 [12] studies, which included data on Spain. Among the possible causes of this situation are factors linked to hypolipidaemic agents, adherence to prescribed treatment and physician-led prescription strategy.

Bearing in mind that over half of all patients with coronary disease and over two thirds of subjects judged to be at high cardiovascular risk fail to attain target lipid values [13], it would seem necessary to implement strategies that enhance adherence to lifestyle changes and compliance with drug therapy. There is evidence of and wide consensus about the benefits of the diet, exercise and drugs to be used, both in primary prevention and in secondary prevention in particular, for the purpose of achieving good control of patients with hypercholesterolaemia.

Among the factors related to adherence to lifestyles and drug therapy in dyslipidaemia, it should be noted that the asymptomatic nature of this disease may contribute to the poor results obtained [7]. Other possible factors are an absence of perception of a risk to health and negligible participation in decision-making [14].

One of the limiting factors in the achievement of targets in hypercholesterolaemic patients is therapeutic non-adherence, which decreases across time [15, 16]. Moreover, such non-adherence should not be taken to refer to medications exclusively, but also to the remaining guidelines. In 2003 the World Health Organization (WHO) defined the term adherence as, “The extent to which a person’s behaviour - taking medication, following a diet, and/or executing lifestyle changes, corresponds with agreed recommendations from a health care provider” [17]. Among dyslipedaemic patients the percentage of non-compliers ranges from 22% to 57% [18], with different studies observing that, in over half of all cases, this is due to forgetfulness when it comes to taking the medication [19]. Other studies have similarly reported a lack of compliance with lifestyle recommendations [20].

Various strategies have been used to improve compliance and, by extension, control of patients. The results of the study conducted by Márquez et al. [21] into the effectiveness of an isolated telephone intervention on compliance with drug treatment, indicated better adherence, yet the patients nevertheless displayed poor control of their dyslipidaemia. This may indicate that improvement in pharmacological adherence alone is not enough to attain designated targets, and that to achieve adequate control, it is essential to follow recommendations other than those which are purely pharmacological. At present, evidence is not being transferred to clinical practice, either here in Spain or in the rest of Europe, and targets are thus not being achieved.

In addition, the strategies that have most improved compliance among subjects with other risk factors, such as hypertension, do not include specific activities, such as pamphlets or telephone alerts, but rather combined activities, such as group sessions coupled with mail-based back-up and support [22], or alternatively, the delivery of printed matter, appointment-reminder telephone calls and mail with educational messages about the disease [23]. In this respect, there would seem to be agreement on the need to use a combination of strategies to improve adherence, thus surpassing the possible benefits of single strategies implemented one at a time [24, 25]. Hence, studies that have used printed information in tandem with individual health education [26, 27] have displayed better results than those that have evaluated just one of these interventions [28, 29], and have successfully managed to increase knowledge about dyslipidaemia and its management. Likewise, strategies exclusively targeted at recording the taking of medication, e.g., telephone calls in the case of dyslipidaemias, have achieved little improvement in compliance [30], with results showing improvement when different reminder combinations have been used [31].

The choice of one method or another should also depend on the population to be targeted and, when it comes to choosing an intervention, consideration should be given to the possible risk entailed in only implementing specific actions that have no continuity and are excessively costly (in terms of time or money) for the expected benefit [32].

In the light of the above, we therefore propose a combined strategy to improve compliance with the recommendations contained in clinical practice guidelines for management of dyslipidaemia, both as to lifestyles (diet, physical activity, alcohol and loss of weight) and as to hypolipidaemic agents. It is a strategy targeted at improving knowledge of dyslipidaemia, increasing compliance with recommendations and facilitating greater patient participation. To this end, a controlled study should be undertaken to examine the effectiveness of such a strategy in terms of adherence to recommendations and control of the cholesterol values of subjects with hypercholesterolaemia.

The proposed study follows the recommendations made by Haynes [33] for studies that assess compliance strategies, inasmuch as it investigates an easily applicable practical intervention, uses a randomised-clinical-trial design, and envisages measuring both therapeutic adherence and the degree of lipid control achieved.

### Study objectives

The main aim of this study is to assess the effectiveness of an intervention designed to improve control of hypercholesterolaemic patients, consisting of a combined strategy that would include the delivery of printed information, text messages and treatment-compliance check cards as complementary measures in support of the intervention at the general practitioner’s (GP) practice.

The secondary objectives would be: 1) to ascertain whether, with respect to routine GP care, the combined intervention strategy improves therapeutic adherence, both pharmacological and non-pharmacological, of hypercholesterolaemic patients, across a follow-up period of 24 months; 2) to ascertain whether, with respect to routine GP care, the combined intervention strategy increases the proportion of patients who attain the low density lipoprotein cholesterol (LDL-C) values set for adequate control, across a follow-up period of 24 months; 3) to quantify the effect of the combined intervention strategy on the remaining lipid-profile-defining parameters, across follow-up; 4) to quantify the effect of the combined strategy on the reduction of cardiovascular risk in patients with hypercholesterolaemia, across follow-up; 5) to identify the factors that contribute to improving the effectiveness of the combined intervention strategy on reducing lipid values, not only in relation to patients’ health status but also in relation to their socio-demographic variables; and, 6) to assess the acceptance and degree of satisfaction of the hypercholesterolaemic patients undergoing the intervention.

## Methods/Design

### Design

Randomised, parallel-group clinical trial in which a group of hypercholesterolaemic patients, undergoing a combined intervention targeted at improving treatment adherence and degree of lipid control as complementary measures in support of the intervention at the GP’s practice, will be compared to another group of hypercholesterolaemic patients who will solely receive routine GP care.

### Study location and subjects

Participants will be recruited from among patients attending family medicine outpatient facilities at 8 health centres situated in three health areas of three of Spain’s Autonomous Regions (Comunidades Autónomas), namely, Castile-La Mancha (Albacete Health Area), Aragon (Zaragoza Health Area) and Galicia (Vigo Health Area). The target population is made up of all persons aged 18 years or over with diagnosis of hypercholesterolaemia, with the population eligible for study comprising hypercholesterolaemic subjects of this age drawn from the eight health centres in the above three participating health areas.

The study inclusion criteria require that candidates: a) be diagnosed with hypercholesterolaemia, as defined according to the criteria stipulated in the cardiovascular prevention guidelines of the 2009 Prevention Activities and Promotion of Health Programme (total cholesterol of 250 mg/dl or higher); and, b) be patients aged 18 years or over attending any of the participating health centres. The following individuals will be excluded: a) any person hindered from participating in the follow-up of the proposed intervention, e.g., illiterate subjects and non-users of mobile telephones; b) any person with a physical disability or impairment which prevents him/her from attending the follow-up visits; and, c) any person suffering from a significant chronic organic or psychiatric disease.

### Sample size

The sample size needed for analysis will be calculated using a two-sided test, based a clinically relevant difference of 20% in the proportion of subjects who attain the lipid control targets, i.e., 55% in the control group, according to data furnished by previous studies (Kotseva et al. [8, 11]; Bueno et al. [18]), and 75% in the group undergoing the proposed intervention. Assuming a statistical power of 90% and an α error of 5%, the estimated sample size would then be 155 subjects in each group (total of 310 subjects). Assuming an expected proportion of losses of 15%, the final size of each group would be 179 subjects (an overall total of 358).

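### The stated 155 patients per group do not follow from the stated inputs: 90% power needs 118 (128 with continuity correction), so the printed power and size disagree

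*Protocol article*

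**What the plan says.** All inputs are in the protocol article, section Sample size. The test is two-sided: "The sample size needed for analysis will be calculated using a two-sided test". The target is "a clinically relevant difference of 20% in the proportion of subjects who attain the lipid control targets", made up of "55% in the control group" and "75% in the group undergoing the proposed intervention". The error rates are given as "Assuming a statistical power of 90% and an α error of 5" per cent. From these the section concludes that "the estimated sample size would then be 155 subjects in each group (total of 310 subjects"). Losses are added afterwards: "Assuming an expected proportion of losses of 15%, the final size of each group would be 179 subjects (an overall total of 358").

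The section names no continuity correction, design effect, multiplicity adjustment or unequal allocation. The 15% for losses is the only inflation mentioned, and it is applied after the 155. The Statistical analysis section plans a chi-squared comparison of proportions, which is the test that the usual two-proportion formula serves.

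**The concern.** An article may leave out its formula. This one prints a complete set of inputs and then a result that those inputs do not produce, so at least one printed figure (power, alpha, difference or size) is not what was used, or a factor was applied and not reported.

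The power statement is what a reader uses to interpret a null result and to judge whether the enrolment was justified. Here the printed power is wrong for the printed size. There is also an unexplained margin, which a reader may credit to something the plan never claimed.

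**Working it through.** **Inputs** (Sample size section): p1 = 0.55, p2 = 0.75, difference d = 0.20, mean p̄ = 0.65, two-sided alpha 0.05 (z = 1.960), power 0.90 (z = 1.2816), equal groups.

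**1. Size at the stated 90% power**

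n = [z_α √(2p̄(1−p̄)) + z_β √(p1(1−p1) + p2(1−p2))]² / d²

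- √(2 × 0.65 × 0.35) = √0.455 = 0.6745
- √(0.55 × 0.45 + 0.75 × 0.25) = √0.435 = 0.6595
- n = (1.960 × 0.6745 + 1.2816 × 0.6595)² / 0.04 = (1.3221 + 0.8452)² / 0.04 = 4.697 / 0.04 = 117.4, so **118 per group**

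With continuity correction:

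n_c = (n/4) × [1 + √(1 + 4/(n d))]²

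- n_c = (117.43/4) × (1 + 1.0818)² = 127.2, so **128 per group**

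The plan's 155 is not reproduced.

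**2. Other standard routes at the stated alpha and power**

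| Method | n per group |
|---|---|
| Unpooled variance | 115 |
| Arcsine | 118 |
| Maximum variance (p = 0.5) | 132 |
| Fisher's exact test | power 0.898 at 125, 0.903 at 128 |
| One-sided test | 96 (106 corrected) |

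None is close to 155. A slip in the 55% alone does not explain it either. With a 20-point difference, 90% power, two-sided 5% and continuity correction, control rates from 1% to 79% give at most 139.1, that is 140 per group.

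**3. Where 155 does appear**

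With power 0.95 (z = 1.6449):

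- n = (1.3221 + 1.0849)² / 0.04 = 5.793 / 0.04 = 144.8, so 145
- continuity-corrected: (144.83/4) × (1 + 1.0668)² = 154.7, so **155**

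The match is exact, but it needs both 95% power and the continuity correction, and the article states neither. Two-sided alpha 0.02 with 90% power and correction gives 156, which is nearly as close.

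**4. Power at 155 per group, patients independent**

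- Standard error under the null: √(0.455/155) = 0.05418; under the alternative: √(0.435/155) = 0.05298
- Uncorrected: Φ[(0.20 − 1.960 × 0.05418)/0.05298] = Φ(1.771) = **0.962**
- Corrected (0.20 reduced by 1/155 = 0.00645): Φ(1.649) = **0.950**
- Fisher's exact test: 0.951

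**5. Size of the gap**

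155/118 = 1.31 and 155/128 = 1.21. The loss allowance starts from 155 (155 × 1.15 = 178.25, so 179), so it does not explain the gap.

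**The case against.** The strongest reply is that the error is harmless. It makes the trial larger than its stated inputs require, so on the section's own independent-patient basis the trial has more power than claimed. No test, estimate or enrolment figure has to change. The target difference, both proportions, alpha and sidedness are all printed, so a reader can see what the trial was meant to detect. All of this stands, and it limits the point to a correction of one statement. It does not remove the contradiction, because 90% power and 155 per group cannot both follow from the other inputs.

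Two stronger readings are tempting, and the article supports neither:

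- **That 95% power was the true design value.** A reader might infer this from the exact match. It holds only with the continuity correction (145 without it), and neither that correction nor 95% power is mentioned. A slip or an unreported allowance cannot be excluded.
- **That the surplus is an allowance for clustering.** A reader might infer this because the Selection of subjects section speaks of randomising by health area. The Sample size section states no such allowance, and the Subject follow-up section has patients randomised at the initial visit. Nothing in the article links the surplus to clustering, and the unit of randomisation is a separate question that this arithmetic cannot settle.

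**Conclusion.** The point holds as an internal contradiction in the Sample size section. The stated inputs need 118 per group (128 with continuity correction), against 155 printed. At 155 the power for 55% against 75% is about 96% (95% corrected), not 90%. These figures assume independent patients, equal groups and outcome data on all 155 per group.

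The discrepancy is conservative and does not by itself leave the trial underpowered. That says nothing about power if outcomes are correlated within areas or centres, which the section's calculation does not address. Which printed figure is the wrong one cannot be settled from the article.

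**What to change.** Keep 358 patients. Check the original calculation, then correct the Sample size section so that power and size agree, in one of two ways:

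- state that 155 per group gives about 95% power (continuity-corrected, patients treated as independent); or
- state that 90% power needs 118 per group (128 with continuity correction) and that the planned 155 exceeds this.

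Name the formula and say whether the continuity correction was used. If the original calculation shows a further factor, report it. Do not describe the surplus as an allowance for clustering unless the records show that it was planned as one.

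The cost is a look at the original calculation and one corrected sentence, with no change in enrolment.

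### The 15% loss allowance does not deliver the plan's own evaluable number: 179 per group less 15% leaves about 152, not 155, with little effect on power

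*Protocol article*

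**What the plan says.** The Sample size section of the protocol article sets out the calculation in one paragraph. The test is two-sided ("The sample size needed for analysis will be calculated using a two-sided test"). The target is "a clinically relevant difference of 20% in the proportion of subjects who attain the lipid control targets", with "55% in the control group" and "75% in the group undergoing the proposed intervention". The error rates are given as "Assuming a statistical power of 90% and an α error of 5"%. From these the section concludes that "the estimated sample size would then be 155 subjects in each group (total of 310 subjects"). It then adds the allowance for losses: "Assuming an expected proportion of losses of 15%, the final size of each group would be 179 subjects (an overall total of 358").

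The Methods/Design part of the abstract repeats the final figure, "covering a total of 358 subjects", so 358 is the trial's working size. The article prints no formula for the step from 155 to 179, and no other section corrects it.

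**The concern.** An allowance for losses is meant to ensure that, if the expected fraction is lost, the number needed for analysis remains. The fraction lost applies to those enrolled, so the enrolled number should be the evaluable number divided by one minus the loss. The printed 179 is instead what results from adding 15% of the evaluable number to itself. A trial that recruited exactly to plan and lost exactly what it expected would then finish below its own stated number for analysis.

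What is at stake is the internal consistency of a planning figure, and possibly power. The article itself names losses over the two-year follow-up as a threat to validity (Discussion), so the allowance should do what it says. Whether power suffers has to be checked separately.

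**Working it through.** **Inputs**, all from the Sample size section: control 55%, intervention 75%, two-sided 5%, power 90%, 155 evaluable per group, losses 15%, final size 179 per group (358).

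**1. Reproducing 179.**
- Multiplying: 155 × (1 + 0.15) = 178.25, rounded up to 179. This matches the printed figure exactly.
- Dividing: 155 / (1 − 0.15) = 182.35, rounded up to 183. This does not match.

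**2. What 179 delivers.**
- Remaining after 15% loss: 179 × 0.85 = 152.15, so about 152 per group. In total 2 × 152 = 304, against the stated 310.
- Largest loss that still leaves 155: 1 − 155/179 = 0.134, or 13.4%.
- The shortfall is 155 − 152 = 3 evaluable per group. In enrolled patients the gap is 183 − 179 = 4 per group, which is 4/183 = 2.2%.

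**3. Does the shortfall matter for power?** Take p1 = 0.55, p2 = 0.75, difference d = 0.20, mean proportion 0.65, and independent patients.

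Power = Φ{[d − 1.960 × √(2 × 0.65 × 0.35 / n)] / √[(0.55 × 0.45 + 0.75 × 0.25) / n]}. For the continuity-corrected version, subtract a further 1/n from d.

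For n = 152, the null standard error is √(0.455/152) = 0.0547 and the alternative standard error is √(0.435/152) = 0.0535. The argument is (0.2 − 0.1072)/0.0535 = 1.734, giving 95.9%.

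| Evaluable per group | Power | With continuity correction |
|---|---|---|
| 152 | 95.9% | 94.6% |
| 155 | 96.2% | 95.0% |

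The slip costs 0.3 to 0.4 percentage points, and both rows lie above 90%.

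**4. Why there is room to spare.** The size that the stated inputs require is

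n = [1.960 × √0.455 + 1.282 × √0.435]² / 0.20² = 117.4, so 118 per group.

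With continuity correction, (117.4/4) × [1 + √(1 + 4/(117.4 × 0.2))]² = 127.2, so 128 per group.

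The unpooled formula gives 115 and the arcsine formula 118. None of these yields 155. The same corrected formula at 95% power does give 155, but the section states 90%.

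**The case against.** The strongest case for leaving this alone is that nothing of consequence follows. Three evaluable patients per group is a 2% matter, and power stays well above target. The 155 that is missed is only a printed figure, since the stated inputs call for 118 or 128, and 152 exceeds both. All of this stands, and it limits the point to a wording correction.

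Two further objections stand in part. First, the article gives no inflation formula, so multiplication by 1.15 is an inference from an exact match. The core of the point does not depend on it: however 179 was reached, 15% off it is not 155. Second, the Statistical analysis section promises an intention-to-treat analysis of all randomised patients, so how many lost patients drop out of the primary comparison depends on missing-data handling that is not shown. That does not repair the sum, because the Sample size section itself budgets for losses as patients unavailable to the analysis.

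A reader might infer more: that the trial is underpowered, or that enrolment must rise to 183 per group (366). The documents do not support either on this ground. Under the plan's own rates, 152 per group exceeds the stated power, and 366 would recruit 8 more people to reach a number that the stated inputs do not require.

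**Conclusion.** The point holds as a minor arithmetic inconsistency. The three figures 155, 15% and 179 cannot all be true: at the expected loss the plan yields about 152 per group (304), 3 per group short of its own number, and 179 protects 155 only up to a 13.4% loss. The stated 90% power is not missed on this account.

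That reassurance rests on the plan's rates of 55% and 75% and on treating patients as independent. The Selection of subjects section describes allocation by health area, while the Subject follow-up section describes randomisation of patients at the initial visit. If allocation is by area, the power figures above do not describe the trial's actual power. That is a separate matter, and it is a reason not to quote about 96% without qualification. The larger unexplained figure in the same paragraph is 155 itself.

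**What to change.** Keep 358 and change one sentence in the Sample size section, in one of two ways:

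- state that 179 per group is expected to leave about 152 evaluable per group (304 in total) after 15% losses; or
- keep 155 and state the tolerated loss as about 13% (179 × 0.87 = 155.7).

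If power is recomputed for 152, say that it assumes independent individuals and takes no account of allocation by health area. In the same edit, explain where 155 comes from and reconcile it with the stated 90% power, so that a figure near 95% or 96% does not stand beside 90% without comment.

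The cost is a sentence or two. The total in the abstract is unchanged, and no additional patients should be enrolled on this ground.
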